**Methods:**

We are conducting a quasi-experimental controlled cluster trial in 4 sites in Spain, Italy, and UK (England, Scotland) over 6 months. We plan to recruit 525, in a 2:1 basis, teenagers aged 13–16 years from secondary schools. The intervention group is provided with the PEGASO system whereas the comparison group continues their usual educational routine. Outcomes include feasibility, acceptance, and usability of the PEGASO system as well as between and within group changes in motivation, self-reported diet, physical activity, sedentary and sleeping behaviour, anthropometric measures and knowledge about a healthy lifestyle.

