### Outcomes and variables

The first block of outcomes that will be assessed are related to recruitment and adherence to the intervention, namely recruitment rate, study retention, adherence to the intervention and attitudes to the different components of the intervention.

We aim to test a range of outcomes related to individual lifestyle (dietary habits, physical activity, sedentary behaviour, and sleeping habits), knowledge/awareness about these health habits and user experience of the platform. Individual lifestyle and knowledge/awareness about health habits are assessed at baseline and at the end (6 months) of the intervention both in the comparison and intervention group. User experience is assessed at month 2, 4 and 6 only in the intervention group. Outcomes, instruments and assessment points during the study are detailed in Table 3.

**Table 3 Tab3:** Outcomes, instruments and assessment points in the PEGASO study

Outcome	Instrument	Assessment point			
		BL	M2	M4	M6
Dietary habits	Mediterranean Diet Quality Index in children and adolescents (KIDMED questionnaire) + 5 additional questions	X			X
Physical activity	Physical Activity Questionnaire for Adolescents (PAQ-A) + 3 additional questionnaires	X			X
Sedentary behaviour	Screen time-based sedentary behavior questionnaire (SSBQ)	X			X
Sleeping habits	Sleep Habits Survey (SHS)	X			X
Knowledge questionnaire	Ad hoc questionnaire	X			X
Anthropometric Measurements		X			X
Height	Stadiometer SECA 213	X			X
WC	Flexible graduated measuring tape (SECA 201)	X			X
Weight	*England, Catalonia, Italy*: Homologated	X			X
BMI	electronic scale Tanita SC240MA				
% of body fat	*Scotland*: Tanita MC780MA Multi	X			X
% of body water	Frequency Segmental Body Composition Analyser	X			X
Family affluence and self-reported health status	Family Affluence Scale (FAS) + 1 question from the Social Functioning subscale −12 (SF-12)	X			
*Motivation*	*Perceived Competence Scale*	*X*	*X*	*X*	*X*
*Usability*	*System Usability Scale*			*X*	*X*
*Emotional Response to the Platform*	*Emotional Metric Outcome questionnaire*			*X*	*X*
*Satisfaction, Trust, Reputation*	Ad hoc *questionnaire*			*X*	*X*
*User Experience*	*Focus Groups*			*X*	*X*

In italics, outcomes assessd only in the intervention group. All the other outcomes were assessed in both, intervention and comparative group

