Motivation to maintain or increase healthy dietary habits and physical activity will be assessed through the “Perceived Competence Scale” a short 4-item scale that assesses the degree to which participants feel confident about being able to make (or maintain) a change toward a healthy behaviour [40]. Adolescents’ age, gender, perceived health status level and family affluence will be included in the on-line questionnaires. Parent’s (or legal guardian’s) educational level, occupation and familiar structure will be also documented only at baseline.

User experience (UX) refers to a person’s total experience using a particular product, system or service [41]. The factors of UX to be investigated during the study include: emotion, engagement, trust, reputation, pleasure/hedonism, usability, acceptability, accessibility, connectedness, context and target behaviours adherence. The PEGASO study aims to holistically assess how the teenagers experience the system in their everyday lives and where and how this experience facilitates use and where it can be improved. Mixed methods (quantitative and qualitative methodology) will be used to assess UX, specifically through self-reported questionnaires and focus groups or semi-structured interviews, respectively. The System Usability Scale (SUS) is a well established 10 item questionnaire with five response options to assess usability of a variety of products and services, where usability is a distinct concept within the overall understanding of UX [42]. SUS will be applied at month 4 to assess usability of the Companion and the game and at month 6 for the whole system. The Emotional Metric Outcome (EMO) questionnaire is a 16 item questionnaire to assess the emotional outcomes of interaction, both positive and negative [43]. The EMO will be undertaken at month 4 and 6. A questionnaire has been created ad hoc in order to measure the satisfaction, trust and reputation of the platform. This comprises a 28 item questionnaire with 5 answer categories and is undertaken at months 4 and 6.

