### Analysis plan and statistical analysis

The analysis plan will include a description of all data at every assessment point and an overall comparison of baseline characteristics between intervention group (IG) and comparison group (CG), as well as by sites and gender. Knowledge/awareness, lifestyles and anthropometric measurements will be compared at pre and post intervention (month 6) utilising an intention-to-treat (ITT) approach, independently from drop-outs and non-adherence. Relevant changes among lifestyles and knowledge will be defined according to current recommendations from international guidelines [46]. The effect of the intervention could be modified by gender, cultural and socioeconomic level, body mass index (BMI), as well as by the baseline lifestyles, which will be controlled in the analysis. Changes in motivation will be assessed in the four assessment points and compared to baseline. For the intervention group, the results from SUS, EMO, satisfaction, trust and reputation questionnaires will be compared from month 4 to month 6. The level of engagement in the PEGASO platform will be assessed from indicators of usage at individual level, such as the number of days of interactions with the APPs or the daily number of steps, stored in the cloud.

Results will be reported as mean ± standard deviation (or median, percentile 25 and 75) for quantitative variables or frequency and percentage distribution for qualitative variables. Quantitative variables will be tested for normality, log-transformed if needed, and accordingly analysed with parametric or non-parametric methods. Chi-squared test will be used to analyse the association between independent qualitative variables, along with the McNemar test for paired samples. The Student t-test will be used for the comparison of means between two groups, and the paired t-test will be applied to assess changes within one same group. Alternatively, the corresponding nonparametric tests will be used, as required. The relationship between quantitative variables will be analysed using Pearson’s correlation coefficient or Spearman coefficient in the case of asymmetrically distributed variables. Techniques of principal component analysis (PCA) will be applied to identify patterns of variables best explaining outcomes of interest.

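### The abstract announces a between-group comparison of motivation, but motivation is measured only in the intervention group, so the plan can give only an uncontrolled change from baseline

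*Protocol article*

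**What the plan says.** The Methods paragraph of the abstract gives as outcomes "between and within group changes in motivation, self-reported diet, physical activity, sedentary and sleeping behaviour, anthropometric measures and knowledge about a healthy lifestyle". Motivation comes first in that list, directly after the words that promise both kinds of contrast. The aims at the end of the Background list three things on which the effect of the system is to be studied: knowledge, motivation and behaviour.

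Under Outcomes and variables, Table 3 has a motivation row measured with the "Perceived Competence Scale" at baseline and months 2, 4 and 6. The row is in italics. The footnote explains the marking: "In italics, outcomes assessd only in the intervention group". It continues: "All the other outcomes were assessed in both, intervention and comparative group".

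The text of the same section describes the scale with the words "Motivation to maintain or increase healthy dietary habits and physical activity will be assessed" and does not say which group completes it. Under Analysis plan and statistical analysis, the plan for this outcome is: "Changes in motivation will be assessed in the four assessment points and compared to baseline".

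**The concern.** The article defines the intervention effect as the change in the comparison group set against the change in the intervention group, expressed as Cohen's d. A reader of the abstract and aims will expect that contrast for motivation. If only the intervention group is measured, the contrast has no second term.

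What is left is a before-after change over six months of school, on a scale given four times to the same pupils. A rise or fall could come from the intervention, from the passage of time, or from answering the same items repeatedly, and the data would not tell these apart. A report that followed the abstract could then present such a change as an effect of the system.

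**Working it through.** No arithmetic applies, because the question is which group is measured. The places to compare are these.

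1. **Contrast announced.** Abstract: between-group and within-group change, attached to motivation. Background: an effect of the system on motivation is an aim.
2. **Who is measured, by the table.** The motivation row is italic, so by the footnote it applies to the intervention group only. The other italic rows are usability, emotional response, satisfaction/trust/reputation and user experience by focus group. All of those need the platform, so the marking is systematic.
3. **Who is measured, by the text.** Outcomes and variables states: "Individual lifestyle and knowledge/awareness about health habits are assessed at baseline and at the end (6 months) of the intervention both in the comparison" (the sentence then names the other arm as well). Motivation is not named there. The same paragraph places user-experience assessment at months 2, 4 and 6 in the intervention group only. Motivation is the only row of Table 3 with a month-2 mark, which fits the intervention-only reading.
4. **What is analysed.** The pre-post comparison in the analysis plan covers knowledge/awareness, lifestyles and anthropometry. Motivation has its own sentence, with baseline as the only reference.
5. **Other possible sources.** The COM-B self-assessment and the Self-Report Habit Index appear as notifications inside the Companion app (Data collected by the PEGASO system). The comparison group does not receive the app, so neither instrument supplies comparison data.

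Steps 2 to 5 agree with one another and conflict with step 1. With zero comparison-group observations, neither the difference in change nor a Cohen's d between groups exists. Enlarging the trial would not alter that.

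**Coverage of the scale.** The motivation text limits the scale to dietary habits and physical activity. The aim refers to obesity-related lifestyle behaviours, and Table 2 includes sedentary and sleep behaviour among the targets. The scale as described therefore does not reach two of the four behaviour domains.

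**A figure best left out.** One could ask how small a drift would reach p < 0.05 in a paired test. Two thirds of 525 is 350, and 1.97/√350 = 0.105 SD of the change score. That assumes every pupil is retained and that pupils are independent. The article says the target allows for attrition, and recruitment was partly by whole class. The figure is illustrative only, and the point does not depend on it.

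**The case against.** The best defence is that the fault lies in one loose phrase. In the abstract the words about between- and within-group change head a single long list, while the body of the article consistently treats motivation as an intervention-group measure. No between-group analysis of motivation is specified in the body, so no planned analysis fails. The study is also partly preparatory: the sample-size text speaks of informing a future cluster randomised trial, and motivation is not named as primary. This bears on severity and is accepted there. It does not remove the conflict, because motivation is the first item after the phrase and the Background independently makes it an effect aim.

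A second objection concerns timing. Recruitment ran from September to November 2016, follow-up lasted six months, and the article appeared in December 2019. Baseline data for the comparison group can probably no longer be collected. This stands, and it makes the wording change the practical remedy.

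Three stronger readings are tempting, and the article does not support them:

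- A reader might infer that the controlled evaluation as a whole is undermined. It is not. Lifestyle, knowledge and anthropometry are measured in both groups at baseline and month 6.
- A reader might infer that comparison-group data would have settled every rival explanation. Allocation was by class, by school or by first response from volunteers, and participants were not blinded. A comparison group would help with time trend and repeated testing. It would not by itself remove bias from selective dropout or from groups that differ at baseline.
- A reader might infer that motivation for sleep and sedentary behaviour goes wholly unmeasured. The COM-B questionnaire addresses motivation and is completed whenever a new target behaviour is chosen, and such targets can include sleep or sedentary time. It is intervention-only and is not the instrument named for the motivation outcome, but it is there.

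**Conclusion.** The inconsistency is real. As the article stands, the between-group change in motivation announced in the abstract cannot be estimated, and the aim of showing an effect on motivation cannot be answered. Only a within-group change is available, and it cannot be separated from time trend or repeated testing.

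The severity is moderate: one of three stated effect aims is affected, it is not designated primary, and the other between-group comparisons are untouched. The conclusion assumes that the Table 3 footnote correctly records who completed the scale, and everything else in the body agrees with it. An analysis plan not shown here could not repair the point, since no analysis can supply observations that were not collected.

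**What to change.** If comparison-group data collection is still possible, add the 4-item scale to the questionnaires that group already completes at baseline and month 6. Analyse it in the same way as the other comparisons of change between the two groups. The cost is four short items at two existing contacts.

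Otherwise, which is likely given the 2016 recruitment:

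- remove 'between' for motivation in the abstract;
- restate the aim and the analysis as an uncontrolled within-group description over the four assessment points, with no claim of effect;
- note that the scale as described covers diet and physical activity, not sleep or sedentary behaviour.

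This costs a few sentences and weakens one claim. No other outcome or analysis needs to change.

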Self-monitoring of behaviour Feedback on behaviour	Display of stats about user behaviours
Social support	Provision of the possibility to interact with the family doctor

*UI*: User interaction

The innovative key component of the PEGASO system is the behaviour recognition system, which allows detection and evaluation of participants’ real-time behaviour (collected through other components of the PEGASO system). A summary of the obesity-related behaviours targeted by the PEGASO system is shown in Table 2.

**Table 2 Tab2:** Target behaviours of the PEGASO system and behavioural goals

Target behaviour	Behavioural goals
Dietary target behaviours	- Fruit consumption of ≥2 servings (250-375 g)/day
	- Vegetable consumption of ≥2 servings (300-450 g)/day
	- Reduced intake of sugar-sweetened beverages
	- Daily breakfast consumption
	- Reduced intake of fast food
	- Reduced consumption of sweet and salty high-energy snack high-energy
Physical activity target behaviours	- 60 min of daily physical activity of moderate-to-vigorous intensity (i.e. involving energy expenditure over 4 METs)
	- Undertake 12.000 steps/day
	- Daily active transport to and from school
Sedentary behaviour	- less than 45% of after-school time daily spent in sedentary activities (≤1.5 METs)
Sleep behaviour	-Daily sleep duration of at least 8 h

*METs* Metabolic Equivalents

Participants have the opportunity to choose one target behaviour at the time. When selecting a new target behaviour, participants are asked to complete the COM-B questionnaire [30]. The answers for each question subset guide which component of the COM-B behaviour system is adopted to target the content of the behaviour change intervention. For instance, the messaging framework in the PEGASO Companion App selects messages that are associated with participants’ preferences expressed in the COM-B questionnaire. This provides an intervention that is personalised to the different needs of the individual intervention participant.

The PEGASO system was developed using a user-centred design approach aiming to deliver a product and interactions which are attractive to adolescents and which enabled them to connect with their peers.

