#### Serious game

The serious game aims to serve a central role as the motivational component of PEGASO. As such, it needs to entertain and engage the player, whilst utilising the PEGASO system to capture information about lifestyles and provide relevant feedback to encourage positive health behaviour changes. There are two central behavioural mechanisms within the game: 1) An “energy bar”, used up by the player’s actions in the game, and replenished when achieving their behavioural goals such as increased physical activity or improved diet, and 2) the game implements “research” mechanics that require the player to apply and develop their nutritional knowledge of various food sources.

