### Procedures

Eligible participants are introduced to the PEGASO system after they and their parents/guardian provided written and signed consent, and after baseline measurements are collected. Participants are provided with a smart phone (running as OS Android, version from 4.4 to 6.0) with the PEGASO apps installed for the duration of the study.

Given the complexity of the PEGASO system, the components are introduced in two sessions within the same first week. The physical activity monitors are introduced to the participants at the mid-point assessment time at month 4 of the study. This time point was chosen to reduce the burden on the schools and participants, allocating time and resources in addition to the baseline measures, mid-point and follow-up assessment contact points, whilst additionally avoiding conflict with exam timetables and extended holiday periods (e.g. summer break). In addition to familiarising the participants with the functionalities and use of the garment and activity monitors, researchers assist participants in connecting the activity monitors with individual smart phones. All introduction sessions across the four study sites provide a mixture of interactive workshops, educational games, and replicate the method as much as possible within the constraints of the school requirements in different countries.

Participants are offered support during the study to facilitate understanding of how to use the PEGASO system and to trouble-shoot any issues arising. Participants are invited to join a site specific Google Hangout group to allow timely communication with the field researchers who provide solutions to technical issues whenever possible. Teachers at schools are offered a brief training session to be able to answer simple questions related to the use of the PEGASO system. They are asked to direct the participants to the web portal and the FAQ link for questions they cannot answer.

The role of teachers is to support students over the testing period, and to facilitate the communication flow among field researchers, parents and teenagers. During on-site contact points an interaction with teachers is expected; they will have the opportunity to indicate to the field researchers any comments, doubts or conflicts including maladaptive behaviours.

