Additional questions: Research team included additional questions in order to better assess the target outcome in case no validated questionnaire were found

Parent’s undertook an ad-hoc questionanire in order to assess sociodemographic characteristics, Socio Economic Status (SES) and Family structure and living conditions of the family

*WC* Waist Circumference, *BMI* Body Mass Index

*BL* Baseline, *M2* Month 2, *M4* Month 4, *M6* Month6

Individual lifestyle outcomes are measured through on-line questionnaires. Dietary habits are assessed through the KIDMED, a 16 item semi-quantitative food habits questionnaire which aims to assess dietary patterns among children, adolescents and young adults [35]. Additional questions are also included to assess the consumption of fast food and sugar-sweetened beverages, breakfast skipping and snacking behaviour. Physical activity is assessed through the Physical Activity Questionnaire for Adolescents (PAQ-A) [36]. Additional questions and an extra question from PAQ-elementary are included to assess those issues related to PA not covered by the PAQ-A such as transportation to school. Sedentary behaviour is assessed by the screen time-based sedentary behaviour questionnaire (SSBQ) from the Healthy Lifestyle in Europe by Nutrition in Adolescence study (HELENA study), which has been validated among participants in the HELENA study against the use of an accelerometer. Participants are asked to report their habitual time devoted to several sedentary behaviours, mostly related to screen time: (a) TV viewing, (b) computer games, (c) console (video) games, (d) Internet for non-study reasons (hobbies), (e) Internet for study reasons and (f) study time (out of scholar schedule) [37]. Sleeping habits are assessed through four questions about sleep duration from the Sleep Habits Survey for Adolescents (SHSA), a validated self-reported survey that estimates sleep patterns in adolescents [38].

Knowledge/awareness about health habits are assessed through an ad-hoc questionnaire (quiz format) that covers knowledge of dietary habits, physical activity and sleeping behaviour. Most of the questions are from a questionnaire, which is validated in Italy [39] and some others are specifically created.

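### The only sedentary measure taken in both arms lists no phone or tablet item, so screen time added by a phone-based intervention could go uncounted and tilt the comparison towards the intervention.

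*Protocol article*

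**What the plan says.** Table 3 (Outcomes and variables) assigns sedentary behaviour a single instrument, the "Screen time-based sedentary behavior questionnaire (SSBQ", at baseline and month 6. The table note indicates that it is given to both groups.

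The text below the table describes its content as "several sedentary behaviours, mostly related to screen time". It lists "a) TV viewing, (b) computer games, (c) console (video) games, (d) Internet for non-study reasons (hobbies), (e) Internet for study reasons" and finally "f) study time (out of scholar schedule". It adds that this is an instrument "which has been validated among participants in the HELENA study against the use of an accelerometer".

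Table 3 and the same section show extra questions added to the diet questionnaire (KIDMED) and to the physical activity questionnaire (PAQ-A), the latter to cover matters that it misses. None is shown for the SSBQ.

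Under Procedures, "Participants are provided with a smart phone (running as OS Android, version from 4.4 to 6.0) with the PEGASO apps installed" for the length of the study. Under Serious game, "The serious game aims to serve a central role as the motivational component of PEGASO". According to the Abstract and the Comparison group section, the comparison group does not get the system and carries on as usual. The sedentary goal in Table 2 (Intervention) is "less than 45% of after-school time daily spent in sedentary activities (≤1.5 METs".

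**The concern.** The intervention is itself screen use on a handheld device, and the outcome instrument has no explicit place for that device. The added exposure falls in one arm only, and month 6, when the outcome is measured, lies within the intervention period. Any under-reporting of phone time is therefore likely to differ between arms.

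If minutes move from TV, computer or console to the study phone and are not reported under another item, the questionnaire records a fall although the pupil is no less sedentary. If PEGASO use comes on top of other screen time and is not reported, a true rise is missed. Both errors favour PEGASO.

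The Analysis plan section bases the intervention effect on the change in one group against the change in the other, and reduced sedentary time is among the improvements named in the Discussion. A favourable sedentary result could therefore be partly or wholly an artefact of what was asked. No later between-group analysis can recover time that was never asked about.

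**Working it through.** The article gives no figure for sedentary time or phone use, so there is nothing to reproduce. The check compares the listed items with the intervention's components and then works out how far under-capture could shift the result.

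**Step 1: where PEGASO use could be reported.**
- TV viewing (a), console games (c) and study time (f): no natural place for PEGASO use.
- Computer games (b): a pupil might put a phone game here, but the item as listed names a computer.
- Internet for non-study reasons (d): no device is named, so online phone use such as messaging or a social stream could go here.
- Internet for study reasons (e): no device is named either, but PEGASO is not schoolwork.
- Game or diary use that the pupil does not think of as Internet use fits none of (a) to (f) clearly.

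**Step 2: other sources in the article.** App interactions are logged (Data collected by the PEGASO system), but only for users of the system. The bracelet and garment arrive at month 4 (Procedures) and belong to the system, so they give no baseline and no comparison-arm data. Neither source supports a between-arm comparison of total screen time.

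**Step 3: size, on assumed values.** Let
- x = added study-phone use while sedentary, assumed 20-40 min/day;
- half of x displace TV, computer or console time (assumed);
- r = the share of the phone use that is reported under (b) or (d).

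True change in sedentary screen time = x - 0.5x = +0.5x.

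Measured change = -0.5x + rx.

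Error = measured - true = (-0.5x + rx) - 0.5x = -(1 - r)x.

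| r | Measured, x = 20 | Measured, x = 40 | True change | Error |
|---|---|---|---|---|
| 0 | -10 | -20 | +10 / +20 | -20 / -40 |
| 0.25 | -5 | -10 | +10 / +20 | -15 / -30 |
| 0.5 | 0 | 0 | +10 / +20 | -10 / -20 |
| 1 | +10 | +20 | +10 / +20 | 0 |

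(All in min/day. Paired values are for x = 20 / x = 40.)

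Under these assumptions the sign reverses only when r is below 0.5. At r = 0.5 a true rise is hidden, and at r = 1 there is no error.

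**Step 4: displacement from the pupil's own phone.** If PEGASO use replaces time on a phone that the pupil already had, and both are reported in the same way, nothing leaves items (a) to (c). True and measured change are both zero, and no false reduction arises.

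**The case against.** The strongest reply is that the article gives short item labels, not the full wording or the instructions to pupils. Item (d) is not tied to a device and may catch much online phone use, and item (b) may catch some gaming. Pupils may also swap PEGASO for their own phone; the Background itself says that adolescents are rapidly taking up smartphones. All of this stands. It makes the bias possible rather than certain, and its size could be nil.

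The stated accelerometer validation does not settle the matter, because it does not show that phone use introduced by an intervention is captured.

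It can also be said that sedentary behaviour is one of many outcomes, and that the study was sized to inform a future cluster randomised trial (Design and settings). That limits the weight of the point. It does not remove it, because an instrument carried into the larger trial would carry the same gap.

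Two stronger readings are tempting, and the documents support neither.
- A reader might infer that any shift to the phone must read as improvement and reverse the sign of the effect. That holds only for displacement from the measured screens combined with low reporting under (b) or (d).
- A reader might infer that counting homework as sedentary time is a defect. The goal in Table 2 covers after-school activity at or below 1.5 METs with no exception for study, the items are described as only mostly screen-related, and the article states no summed score into which study time would enter.

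**Conclusion.** The point holds as a risk of differential under-capture. The one sedentary measure common to both arms has no explicit phone, tablet or phone-game item and no added question, while one arm alone is given a phone with apps and a game. Any resulting error favours the intervention.

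For an assumed 20-40 min/day of added use, the error runs from zero (all phone use reported under existing items) to the full 20-40 min/day (none reported). With half of the use displacing TV, computer or console time, the measured change runs from -20 to +20 min/day against a true change of +10 to +20. These values illustrate the mechanism and are not estimates: usage, displacement and reporting share are all unknown from the document.

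The concern is limited to the sedentary outcome. It is worth addressing because the remedy is small and the direction of any error is predictable.

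**What to change.** Add one item in the SSBQ format on smartphone and tablet time, covering games, apps and messaging and including PEGASO, at baseline and month 6 in both arms. Alternatively, tell pupils in both arms under which existing item to report phone use. Report the original SSBQ score alongside any extended total.

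The cost is one online question, or one line of instruction, at two existing assessments. The downside is that the extended total is no longer the validated score, which is why both should be shown.

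Recruitment ran from September to November 2016, follow-up was 6 months and the article appeared in December 2019, so data collection has probably ended. In that case, limit the sedentary conclusion to the listed activities, say that phone time was not asked about explicitly, and show logged PEGASO use next to the intervention-arm result. The logs cover one arm and only PEGASO use, so they inform interpretation but cannot correct the comparison. The added item then belongs in the future trial.
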